### Sample Size

Frailty occurrence in people living with HIV or AIDS represents a binary outcome. Previous studies reported a frailty incidence of 59.3% in hospitalized older adults living with HIV or AIDS, which was assessed using the FRIDE frailty scale [16]. Due to the current lack of a frailty prediction model for HIV/AIDS patients, it is not possible to determine *R*^2^ through previous models. Based on the proportion of outcome events, the maximum *R*^2^ (*R*^2^ cs_max) is calculated to be 0.7416. Assuming that the new model can explain 20% of the variability, the expected *R*^2^ is 0.1483 (=0.7416×20%). We expect the predictive model to include 5 to 10 predictor variables, based on “pmsampsize(type=‘b’, csrsquared=0.1483, parameters=10 , prevalence=0.593).” In this formula, csrsquared represents the ability of the expected prediction model to explain outcome variability; parameters represent the total number of candidate variables expected to be included; and prevalence refers to the prevalence of frailty events in older people living with HIV or AIDS in China based on previous research. The calculation indicates that a minimum sample size of 556 is required. A total of 330 events were expected, corresponding to 33 events per predictor variable. The above results are calculated using the pmsampsize package in R Statistical Software (version 4.4.0) [17].

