### Prediction Variables

#### Determination of Candidate Variables

The selection of predictive variables for this prediction model is based on a review of literature and consensus opinions by an expert group, taking into account its practicality in clinical settings. Possible clinically relevant variables will be selected as candidate predictors of frailty and evaluated after the patient’s admission examination is completed. Through 3 group discussions and 1 online expert consultation meeting, a total of 31 candidate predictor variables were identified and classified into physiological, psychological, and environmental factors based on TOUS. The variables to be explored are detailed in the following subsections.

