### Model Development and Validation

The sample size of this study is relatively small. This study uses logistic regression (LR) as the benchmark for performance comparison. LR has certain advantages in handling limited sample sizes and can demonstrate feature coefficients and significance levels. Although random forest (RF) has the risk of overfitting in small sample situations, it has certain advantages in handling complex nonlinear relationships. We will minimize the risk by adjusting decision tree parameters and cross-validation. Support vector machine (SVM) is particularly suitable for handling situations with high feature dimensions but relatively small sample sizes, and its regularization properties help control the risk of overfitting. As one of the tree ensemble algorithms, XGBoost also has the risk of overfitting and relatively complex parameter tuning. Neural networks have high requirements for sample size and poor clinical interpretability for small sample studies. We hope to ensure the robustness of the model to a large extent in this small sample study. For future larger-scale research, more complex machine learning methods will be used.

Randomly split the training set and validation set in a 7:3 ratio, and use the following machine learning algorithms for modeling: LR model, RF, and SVM. Univariate analysis combined with least absolute shrinkage and selection operator regression will be used to screen predictive factors. To address nonlinearity, we will analyze the relationships between relevant factors and HIV frailty risk using restricted cubic splines and incorporate them as spline terms in the model. Restricted cubic splines can also indirectly capture potential interactions between features. Interactions and complex nonlinear decision boundaries will be handled by selecting nonlinear kernel functions in SVM. The primary model performance evaluation metric is accuracy, which represents the proportion of correctly predicted samples in classification tasks. This will be considered alongside precision, recall, *F*_1_-score, and area under the receiver operating characteristic curve for comprehensive assessment. Through integrated comparison, the algorithm achieving optimal balance across these metrics will be selected as the final model for predicting frailty status in people with HIV.

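### The sample size is computed for 10 parameters, the expected final model size, although 31 candidates are screened on the study data; 556 and 33 events per predictor do not describe this design

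*Protocol article*

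**What the plan says.** The Sample Size section starts from a frailty proportion of 59.3%, a maximum Cox-Snell R² that "is calculated to be 0.7416", and the assumption that the model explains 20% of the variability, so that the expected R² is 0.1483. The call uses "csrsquared=0.1483, parameters=10 , prevalence=0.593". The value 10 comes from the expectation that the predictive model will hold 5 to 10 predictors. The next sentence nevertheless defines the argument differently: "parameters represent the total number of candidate variables expected to be included". The section concludes that at least 556 patients are required, and adds: "A total of 330 events were expected, corresponding to 33 events per predictor variable".

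Under Determination of Candidate Variables, "a total of 31 candidate predictor variables were identified and classified into physiological, psychological, and environmental factors". Model Development and Validation then screens predictors by univariate analysis combined with LASSO. It also examines nonlinear relationships with restricted cubic splines and will "incorporate them as spline terms in the model".

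On the number of patients used to build the model, Patient Recruitment gives 445 for development and 111 for validation, while Model Development and Validation gives a 7:3 random split.

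**The concern.** The criterion behind the calculation asks how many patients keep overfitting within a set limit for a given number of parameters considered. When the data choose the predictors, every candidate offered to the selection step adds to the overfitting, not only those retained. Entering the final model size therefore understates the requirement, and it also conflicts with the article's own definition of the argument.

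Two published figures depend on this input: the minimum of 556 and the 33 events per predictor. A reader would take them to mean that the model is well supported by the data. If the true ratio is about a third of that or less, an unpenalised model built on the selected variables would be expected to give risks that are too extreme. The metrics named in the Abstract and under Model Development and Validation (accuracy, precision, sensitivity or recall, specificity, F1, AUC) include no calibration measure, so this could go unseen.

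**Working it through.** **Inputs.** Prevalence φ = 0.593, R² = 0.1483 and P = 10 (all from Sample Size); 31 candidates (Determination of Candidate Variables); development sizes 445 (Patient Recruitment) and 0.7 × 556 ≈ 389 (Model Development and Validation). The shrinkage target S is not given in the article.

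**Reproducing 556.** For a binary outcome the method takes the largest n from three criteria.

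1. Shrinkage: n = P / [(S − 1) ln(1 − R²/S)]. With S = 0.9, ln(1 − 0.1483/0.9) = −0.18006, so n = 10 / (0.1 × 0.18006) = 555.4, rounded up to 556.
2. Small optimism in R²: the same formula with S = R² / (R² + 0.05 × max R²) = 0.800 gives 244.
3. Precision of the overall risk: (1.96/0.05)² × 0.593 × 0.407 = 370.9, rounded up to 371.

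The largest is 556. Events: 0.593 × 556 = 329.7; per parameter, 329.7/10 = 33.0. Both published figures reproduce. With P = 10, other targets in criterion 1 give 244 (S = 0.80), 348 (S = 0.85) and 1,179 (S = 0.95), so 0.9 is the value behind 556. The maximum R² computed from φ = 0.593 is 0.7411 rather than 0.7416, a difference that does not matter here.

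**Changing only P.** With P = 31, criterion 1 gives 31 / 0.018006 = 1,721.7, rounded up to 1,722 (about 1,021 events). The stated minimum is 556/1,722 = 32% of this.

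**How many candidates?** The article does not number the 31. Counting the listed variables with the comorbidities as one item, each scale once and the anxiety and depression scale as two gives 14 sociodemographic, 4 disease-related, 3 for sleep, nutrition and cognition, 2 psychological, 1 social support and 4 laboratory variables, or 28. Adding IL-6, sTNFR1 and sTNFR2 gives 31, but Data Acquisition says that these three were not collected. Counting the eight comorbidities separately gives 35 collected variables. So 28 to 35 is a fair range:

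| P | n for S = 0.9 | n=556: events per candidate; S | n=445 | n=389 |
|---|---|---|---|---|
| 10 | 556 | 33.0; 0.900 | 26.4; 0.878 | 23.1; 0.864 |
| 28 | 1,556 | 11.8; 0.766 | 9.4; 0.725 | 8.2; 0.698 |
| 31 | 1,722 | 10.6; 0.748 | 8.5; 0.705 | 7.4; 0.677 |
| 35 | 1,944 | 9.4; 0.725 | 7.5; 0.680 | 6.6; 0.652 |

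S at a fixed n is criterion 1 solved for S. Events are 0.593 × n: 329.7, 263.9 and 230.7.

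Dummy and spline terms would raise P further. Their number is not given; assumed totals of 40 and 50 parameters would need 2,222 and 2,777 patients.

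**Other checks.** If all 603 patients recruited by December 5, 2025 were used for development, P = 31 would give 357.6/31 = 11.5 events per candidate and S = 0.76. To keep S = 0.9 at n = 556 with P = 31, R² would have to be about 0.385, or 52% of the maximum, against the 20% assumed.

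**The case against.** - **The arithmetic of 556 is right, and 33 is true for 10 predictors.** Both stand. The fault is in the input. If the final model size was meant, the definition of the argument is wrong; if the definition is meant, the 10 is wrong.
- **The 0.9 target is not in the article.** True. It is inferred because it returns 556. A reader might infer that the protocol promises a shrinkage of 0.9 or good calibration; it makes no such promise. The mismatch of 10 with 31, and of 33 with 10.6 events, does not depend on it.
- **Some of the 31 cannot enter a model.** This is possible for the three uncollected markers, which is why a range is given. At 28 candidates the requirement is still 1,556.
- **The plan has other safeguards.** A reader might infer that the sample size is the only protection against overfitting. The article does not support that: it plans LASSO, regularised support vector machines, repeated 10-fold cross-validation with tuning, a limit on the AUC gap, bootstrap resampling and a temporal validation sample. These measure or limit overfitting. They do not make the published figures true, and the sample size calculation takes no credit for them.
- **The shrinkage formula is an approximation here.** It does not model screening by univariate tests and LASSO, so the values of S indicate the scale of the problem and do not predict an exact calibration slope.
- **Coding of categorical variables may be left to the analysis plan.** Accepted. The main figures therefore count variables only, and extra terms are shown as an assumption.

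**Conclusion.** The point holds as an inconsistent input to the sample size calculation. On the article's own definition and its own candidate list, the method used returns 1,722 patients (1,556 to 1,944 for 28 to 35 candidates, before dummy and spline terms), not 556. The 33 events per predictor applies only to 10 parameters at n=556. With 31 candidates it is 10.6 at n=556, 8.5 at n=445 and 7.4 at about 389, with expected shrinkage of about 0.75, 0.71 and 0.68. This rests on R² = 0.1483, prevalence 0.593 and the inferred target of 0.9.

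A reader might infer that the study must recruit about 1,700 patients or cannot proceed. That does not follow. What is wrong is the stated justification, and the consequence is a model that needs shrinkage and a calibration check. A reader might also infer that limiting the list to 10 parameters would make 556 correct. It would not, because 556 is a development minimum and only 445 or about 389 patients are used for development.

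**What to change.** Make these changes before any analysis; the Results section says that none has been done.

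1. In Sample Size, set the argument to the actual number of candidate parameters: the collected variables plus their dummy and spline terms.
2. Report events per candidate parameter and expected shrinkage at the development sample size that will really be used, and state the shrinkage target.
3. Withdraw the statements that 556 is the required minimum and that there are 33 events per predictor.
4. Make the final logistic model a penalised (shrunken) fit instead of an unpenalised refit of the selected variables, and report its calibration slope with the other metrics.

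Reducing the candidate list without looking at the outcome is optional. It would pull against the objective of identifying associated factors, and even 10 parameters gives an expected shrinkage of only 0.88 at n=445 or 0.86 at n=389.

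The cost is a less favourable published figure and slightly more analysis work. No further recruitment is needed.

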### Definition of Outcomes

At present, the frailty assessment methods adopted in various domestic studies are inconsistent, and there are significant differences in research results. Most studies use a single physiological dimension frailty scale (such as frailty phenotype). We believe that frailty phenotype, as a universal frailty assessment tool including core indicators such as weight loss and perceived fatigue, may be affected by HIV-specific factors. For example, a decline in immune system function leads to the occurrence of opportunistic infections, as well as nausea, vomiting, diarrhea, and nutrient absorption disorders caused by the side effects of most antiviral drugs, which makes people living with HIV or AIDS more prone to weight loss. In addition, most antiretroviral drugs cause patients to experience fatigue and exhaustion, which may exacerbate physical inactivity. Current research on multidimensional frailty is expanding. Global studies have confirmed the strong applicability of the Tilburg Frailty Indicator in people living with HIV or AIDS [18,19]. Its comprehensive advantage in assessing frailty across physical, psychological, and social domains may render it more suitable for the objectives of this study than unidimensional tools.

The main outcome of this study is the presence of frailty among people living with HIV or AIDS. We use the Tilburg Frailty Indicator for reporting, developed by Gobbens et al [20] and localized by Li et al [21]. The scale consists of 15 items, with physiological dimensions including 8 items: physical health, natural weight loss, walking difficulties, balance, vision, hearing, grip strength, and fatigue; the psychological dimension includes 4 items: memory, depression, anxiety, and coping ability; and the social dimension includes 3 items: living alone, social relationships, and social support. If the patient’s current condition meets the description of 5 or more items, it indicates that the patient has frailty. The final assessment results of the scale will be confirmed by 2 specialists in infection and immunology.

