#### Physiological Factors

The sociodemographic data assessed included age, gender, marital status, place of residence, education level, work situation, average monthly income, medical payment method, height, weight, BMI, smoking history, alcohol consumption history, and exercise status [22-25].

Disease-related conditions include time of HIV diagnosis, start time of antiviral treatment, route of infection, and the types of diseases that have been diagnosed at present and other associated complications (heart failure, hypertension, cerebrovascular disease, diabetes, moderate or severe liver disease, moderate or severe kidney disease, chronic obstructive pulmonary disease, and tumors) [26-29].

The Pittsburgh Sleep Quality Index (PSQI) developed by Buysse is used for collecting sleep data [30,31]. It includes 7 dimensions: sleep quality, bedtime, sleep duration, sleep efficiency, sleep disorders, hypnotic drugs, and daytime dysfunction, totaling 18 items. Each dimension is scored from 0 to 3 points, with 0 indicating the absence of sleep disorders, 1 indicating mild disorders, 2 indicating moderate disorders, and 3 indicating the presence of severe disorders. The total score ranges from 0 to 21, with a PSQI >7 indicating sleep problems.

Nutritional status is assessed using the Mini Nutritional Assessment-Short Form scale developed by Rubenstein and consists of 6 items, including changes in appetite, weight, mobility, activity, mental health status, and BMI index [32,33]. The total score is 0 to 14 points, with <8 points indicating malnutrition, 8 to 11 points indicating a risk of malnutrition, and ≥12 points indicating good nutritional status. Research has shown that this scale has good sensitivity and specificity in China [34].

Neurocognitive function is evaluated using the International HIV Dementia Scale, a rapid screening tool developed by Sacktor et al [35,36,37]. It can screen for psychomotor speed, attention, working memory, executive function, and language. Including 3 tests with a total score of 12, patients with a score of ≤10 should be further evaluated for possible dementia. Studies have shown that the International HIV Dementia Scale has better efficiency in detecting the neurocognitive performance of patients using antiretroviral drugs [38].

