#### Psychological Factors

The Hospital Anxiety and Depression Scale is used for anxiety and depression [39,40]. Mainly used for screening anxiety and depression status of patients in hospitals. The Hospital Anxiety and Depression Scale is divided into 7 anxiety items and 7 depression items. Each item is scored from 0 to 3 points, with higher scores indicating more severe anxiety and depression. This scale has good reliability and validity in the application of people living with HIV or AIDS in China [41,42].

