#### Social Factors

The Chinese version of the Social Support Rating Scale developed by Xiao [43] is used to measure an individual’s social support status, including three dimensions: objective support, subjective support, and personal utilization of social support [44,45]. There are a total of 10 items, with a total score of 12 to 66 points. The higher the score, the higher the level of social support. A general total score of ≥45 indicates a high level of support, 23 to 44 indicates a moderate level of support, and ≤22 indicates a low level of support. Social Support Rating Scale is widely used in people living with HIV or AIDS [46].

Laboratory examination indicators were HIV load, CD^4^ T lymphocyte count, albumin, C-reactive protein (CRP), interleukin-6 (IL-6), and soluble tumor necrosis factor receptors (sTNFR1 and sTNFR2) [47-50]. It is worth noting that although inflammatory indicators such as IL-6 and sTNFR1/2 are potential predictive factors for hospitalized older adults living with HIV or AIDS, these items do not have clinical applicability due to their noninfectious and immunological routine clinical testing content, and relevant test results cannot be obtained.

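### Several candidate predictors overlap in content with items of the Tilburg outcome, so the associated factors (aim 2) and the AUC (aim 3) are partly circular

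*Protocol article*

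**What the plan says.** **Outcome (protocol article, Definition of Outcomes).** The main outcome is frailty on the 15-item Tilburg Frailty Indicator. The 8 physical items are "physical health, natural weight loss, walking difficulties, balance, vision, hearing, grip strength, and fatigue". For the second domain the article states: "the psychological dimension includes 4 items: memory, depression, anxiety, and coping ability". For the third domain it states: "the social dimension includes 3 items: living alone, social relationships, and social support". The cut-off is: "If the patient’s current condition meets the description of 5 or more items, it indicates that the patient has frailty".

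**Candidate predictors (Physiological, Psychological and Social Factors).**
- "The Hospital Anxiety and Depression Scale is used for anxiety and depression".
- The SSRS covers "objective support, subjective support, and personal utilization of social support".
- The MNA-SF "consists of 6 items, including changes in appetite, weight, mobility, activity, mental health status, and BMI index".
- Of the International HIV Dementia Scale the article says: "It can screen for psychomotor speed, attention, working memory, executive function, and language".

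**Timing.** Under Patient Recruitment, all assessments fall within the hospital stay. Under Data Acquisition, the frailty, anxiety and depression, nutrition and support scores all come from questionnaires given face to face. The Discussion calls the study cross-sectional.

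**Use.** Aim 2 is to identify factors associated with frailty and aim 3 is to build and validate a prediction model. Predictors are screened by univariate analysis and LASSO. The limitations discussed are missing biomarkers, the single centre and the lack of causal inference. Overlap between predictors and outcome is not mentioned.

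**The concern.** A scale that measures a component of the outcome will be associated with the outcome whether or not it says anything about the rest of frailty. With predictors and outcome taken in the same stay, there is no time order that would make earlier distress or poor support a forerunner of later frailty.

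**Aim 2.** Anxiety, depression, low support or weight loss could be reported as factors associated with frailty when they are partly its definition.

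**Aim 3.** Univariate screening followed by LASSO favours variables strongly correlated with the outcome, so the overlapping scales are likely to be retained and part of the AUC will reflect shared content. Cross-validation, the bootstrap and the temporal validation sample cannot show this, because the same overlap is present in every resample and in every new patient.

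Aim 1, the prevalence estimate, is not affected.

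**Working it through.** **1. The plan's own figure.** Inputs from Sample Size: R²cs 0.1483, 10 parameters, prevalence 0.593. With the usual target shrinkage of 0.9, n = 10 / [(0.9 − 1) × ln(1 − 0.1483/0.9)] = 555.4, rounded up to 556. Expected events are 556 × 0.593 = 329.7, about 330, or 33 per predictor. The stated figures reproduce, and this point does not dispute them.

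**2. Overlap count.**

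| Tilburg item | Candidate scale | Match |
|---|---|---|
| Depression | HADS depression | clear |
| Anxiety | HADS anxiety | clear |
| Social support | SSRS | clear |
| Weight loss | MNA-SF weight change | clear |
| Walking difficulties | MNA-SF mobility | loose |
| Memory | HIV dementia scale, working memory | loose |
| Social relationships | SSRS | arguable |

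This gives 4 clear matches, 6 with the loose ones, and 7 with the arguable one.

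**3. What overlap alone could do (illustration).** Assumptions, none of them in the document:
- The 15 items are independent with equal prevalence q. Solving P(at least 5 of 15) = 0.593 gives q = 0.332.
- Each overlapped item has a proxy that keeps the item's value with probability κ and is otherwise redrawn with probability q, so κ is the chance-corrected agreement.
- The predictor is the sum of the proxies.

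Under independence, nothing but overlap can be predicted, and the AUC without overlap is 0.50.

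| Agreement κ | AUC (R²cs), 4 items | AUC (R²cs), 6 items |
|---|---|---|
| 1.0 | 0.73 (0.17) | 0.79 (0.26) |
| 0.8 | 0.68 (0.11) | 0.73 (0.16) |
| 0.6 | 0.64 (0.06) | 0.67 (0.09) |
| 0.4 | 0.59 (0.03) | 0.61 (0.04) |

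**4. Benchmark.** For a normally distributed linear predictor at prevalence 0.593, R²cs = 0.1483 requires an SD of 0.92 and gives an AUC of 0.726. On the R²cs scale, overlap alone therefore ranges from 0.027/0.148, under a fifth of the planned value (4 items, κ = 0.4), to more than all of it (6 items, κ = 0.8 or above).

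**5. Reaching the cut-off on overlapped items alone.** With 6 items, P(at least 5 of 6) = 0.018, so 1.8% of patients, or 0.018/0.593 = 3% of frail patients. With 4 items it is impossible. The more telling figure is how many frail patients depend on the overlapped items. P(at least 5 of the other 9) = 0.143, so 1 − 0.143/0.593 = 76% of frail patients would fall below 5 without those six.

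**6. Effect of removing items while keeping the cut-off of 5.** P(at least 5) falls from 59% with 15 items to 52% with 14, 45% with 13 and 37% with 12.

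**The case against.** **These are separate instruments.** No shared item is shown. The dementia scale consists of performance tests, and mobility in the MNA-SF is not shown to be the same as walking difficulty. This stands: a reader might infer that predictors duplicate six outcome items, but the document supports only shared constructs, four of them clear.

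**The AUC is not biased.** It validly estimates how well these scales classify Tilburg 5 or more in new patients. This also stands: a reader might infer optimism or inflation in the technical sense, but the problem is what the AUC means.

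**The illustration is generous.** It uses item-level copies, whereas the plan describes multi-item scales with total scores or cut-offs, and weight and mobility are only two of six MNA-SF components. Agreement of 0.8 between one Tilburg item and a different scale is unsupported. This stands and limits the size claim.

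**Dropping the scales would gut the framework.** Without HADS the psychological domain is empty, and without the SSRS so is the environmental domain as the Abstract describes it. This is a fair reason not to insist that the primary model exclude them.

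**Sensitivity models may sit in an unseen analysis plan.** They may, but the outcome and candidate list are fixed in this article, and its account of validation and limitations leaves the overlap out. Conceding that causal relationships cannot be established does not answer it: shared content is a different problem from causality.

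**Conclusion.** The concern holds as partial circularity. Four clear and up to 6 or 7 of the 15 outcome items share content with candidate scales measured in the same admission, and the planned validation cannot reveal it. The associated factors under aim 2 and the meaning of the AUC under aim 3 are affected.

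The size is uncertain. Overlap alone gives an AUC of 0.59 to 0.73 with 4 items and 0.61 to 0.79 with 6, against about 0.73 implied by the planned R²cs. These values rest on independent items, equal item prevalence and assumed agreement of 0.4 to 1.0.

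A reader might infer that overlap would supply most or all of the planned performance; that is only the upper end of the range. A reader might also infer that patients are commonly classed as frail on overlapped items alone; in the illustration that is 1.8% with six items and none with four, although correlated items would raise the six-item figure.

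**What to change.** The Results section says no data analysis has been done, so these can still be prespecified.

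1. **Aim 2.** Beside the full-score result, test each overlapping scale against the Tilburg score without its matching items: HADS without depression and anxiety; SSRS without social support (and social relationships, if counted); MNA-SF without weight loss and walking; the dementia scale without memory. Analyse the reduced score as a continuous or count variable. Keeping the cut-off of 5 would change prevalence and make the results not comparable.
2. **Aim 3.** Report a prespecified model without the overlapping scales beside the full model, and label the full model as containing outcome components. Which of the two is primary is a judgement for the sponsor, given the theoretical framework.
3. **Limitation.** State the overlap, separating clear from loose matches.

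**Cost.** A few extra analyses of the item-level Tilburg answers, with no new data collection. Associations will probably be weaker and the AUC lower in the non-overlapping versions.
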